## Abstract

**Background:**

Cerebral palsy (CP) is the most common lifelong physical disability in the UK and is linked to multiple social, psychological and health inequalities which are often amplified as this group ages. Most middle-aged and older people with CP are supported in their community by General Practitioners (GPs) and complain of disjointed and non-specialised care from people who have a poor understanding of their complex ageing needs. This points to the need for specialised holistic care for this group. Therefore, there is a pressing need to develop ways to support people ageing with CP within their communities.

**Project aim:**

To evaluate a co-developed specialised CP link worker role to support adults aged 40 and older ageing with CP in North Central London over 1 year.

**Methods:**

We will undertake an evaluation of the link worker role by gathering data at baseline, 1-week and 3-months from participants who use the service. Feasibility outcomes will include recruitment and retention rates, acceptability of the intervention, completeness and quality of outcome data, and the practicality of collecting and analysing participant-reported outcome measures. Process evaluation outcomes will include insights into how the intervention was delivered and received, fidelity to the intervention model, contextual factors that influenced implementation, potential sustainability, and stakeholder experiences. This project has been co-developed with the charity UP – The Adult Cerebral Palsy Movement, and we will work alongside a lived experience advisory group and stakeholder advisory group throughout the project.

## Introduction

There are 130,000 adults ageing with cerebral palsy (CP) in the UK, and existing research suggests this group experiences lifelong issues with multiple social determinants of health including decreased social participation, lower employment, social exclusion, discrimination, and a lack of access to specialised health services in adulthood [1–5]. A lifetime of inequality increases the risk of developing physical, social, and mental health issues as people with CP age.

Adults ageing with CP are more likely to develop serious physical age-related issues at much earlier ages than we see in the general population. In their late 30s and early 40s it is common for people with CP to require joint replacements, experience multiple falls and need to use mobility aids [6,7]. Alongside this we observe people with CP being more likely to develop a range of age-related health issues much earlier such as heart and respiratory diseases, diabetes, arthritis, and dementia alongside the worsening of lifelong symptoms such as pain and fatigue [8–11]. These physical health issues can exacerbate social and mental health difficulties for older adults with CP. Issues such as loneliness [12,13] social isolation and social exclusion [14] and mental illness [15] are all commonly reported in this ageing population.

These complex physical, social, and mental health issues point to the need for specialised support. In childhood people with CP are often supported by specialist teams, however, once people reach adulthood they are often discharged from these services and transitioned to non-specialised care; something that many people with CP struggle with [16]. At this point it is a primary care clinician (referred to as a General Practitioner (GP)  in the UK) rather than a specialist clinician who becomes the main point of contact and healthcare support for adults with CP in the UK [3]. Although research has focused on the ways to support adults making the transition from specialised childhood care to non-specialised adult care [16,17], there remains little understanding of the meaningful ways we can support older adults with CP who are relying on non-specialist support within their community. As the GP is the main healthcare contact for adults with CP, there is a need for us to look to innovative ways to aid primary care in supporting this ageing population within the community.

We are framing our project through a lens of healthy ageing, a process that allows people to maintain their wellbeing in older age through maintenance of functional ability [18]. To enjoy a good older age, it is important that people have the lifelong support needed to age healthily – physically, socially, and mentally. However, the health inequalities experienced by people with CP suggest we need to develop better ways to support this group to age well. Social prescribing is one way we could support people with CP within their community to promote their health and wellbeing and reduce health inequalities.

Social prescribing aids emotional, social and practical needs [19] and includes being referred/introduced by a link worker to specific/organised activities such as befriending, volunteering opportunities, supported education, creative arts, physical activity, and support with employment or legal advice. There are ongoing studies that are piloting and testing the feasibility of specialised link worker roles for populations such as those with depression, cancer and pain [20–22]. Therefore, there is a unique and timely opportunity for us to develop a link worker service specifically targeted at the needs of adults ageing with CP.

While there are some specialist centres that support adults with CP in the UK, these are often in tertiary centres and people cannot rely on these services for day-to-day support for their wellbeing. There is a need for us also to consider how we can implement specialised support that will be more readily accessible to people ageing with CP within their own community.

As such, the overarching aim of this project is to assess the feasibility and acceptability of delivering a link worker intervention for middle-aged and older adults with CP living in North Central London, including the feasibility of collecting outcome data. It also aims to conduct a process evaluation to explore how the intervention is delivered, received, and shaped by contextual factors. We have the following specific objectives:

1.) Establish the reach, retention, dose, fidelity, acceptability, potential sustainability, contextual influences, and any unintended consequences of the intervention.2.) Document the type and range of community-based groups and activities prescribed by the CP link worker to participants.3.) Identify and explore the experiences and engagement of participants and key stakeholders involved in the delivery of the intervention.4.) Evaluate the methodological and procedural aspects of the intervention, including recruitment strategies, consent procedures, and data collection methods.5.) Assess the suitability of the selected outcome measures for evaluating the impact of the intervention.

## Methods

### Co-design of project

This project has been co-developed with the charity UP – The Adult Cerebral Palsy Movement (UP) [23]. UP are a highly research active charity who are keen to develop research that will have direct impact on the lives of adults with CP. UP have highlighted the disparate and lack of joined up care for adults with CP, particularly those older adults with CP whose health needs have worsened. They state that most older adults with CP are supported by GPs who do not understand their unique and heterogeneous ageing needs. They also emphasise that there are potentially many resources that could be available within the community to support older adults with CP, but that these need to be mapped, and there needs to be a way to signpost older adults with CP to these services. Finally, they state that adults ageing with CP and healthcare providers are not always aware of how CP might impact them as they get older, and that a link worker could have an important role in educating both adults with CP, GP’s and their broader communities about the impact of ageing. Thus, we opted to pilot a specialised link worker role over other potential interventions as when we have spoken to adults with CP, they are keen that they receive person-centred support for their ageing needs.

### Patient and Public Involvement (PPI)

Alongside working with UP as project partners we are also working closely with two advisory groups. Our lived experience advisory group consists of 6 adults with CP who are advising on the implementation of the project. The group will meet regularly over the course of the project and advise on key aspects of the project such as interview and questionnaire development, study recruitment, aiding the interpretation of study data and helping develop a project dissemination plan. Our stakeholder advisory group consists of 4 healthcare professionals working with adults with CP and people who work in social prescribing. This group supports the team with ideas for recruitment, development of training resources for the link worker, dissemination and advising on post-project implementation. Alongside these groups we have involved additional adults with CP (n = 5), link workers (n = 4) and health and social care professionals (n = 5) in co-development workshops over Summer 2025 to develop training for the link worker and give advice on project implementation.

### Enhancing accessibility

To enhance accessibility of the study we will produce easy-read versions of all participant documents. We will also produce large font versions of materials. The need for alternative language materials will also be assessed and met throughout the project by working with professional translation services (including British Sign Language). Participants will be offered alternative options for data collection including online, by phone, hard copy or in person.

### Intervention study

#### Design.

This study is a feasibility study with integrated process evaluation which will collect both quantitative and qualitative data.

#### Participants and recruitment.

Two pools of participants will be recruited: – (a) adults with CP who take part in the intervention and (b) key stakeholders and supporters who have been involved in the development or delivery of the intervention.

For the intervention sample we will recruit adults with CP aged 40 and older living in North Central London (NCL, i.e., the boroughs of Barnet, Camden, Enfield, Haringey, and Islington) who have capacity to consent, or their carer/ supporter responding on their behalf. We aim to recruit a minimum of 31 adults with CP to the intervention. Sample sizes between 12 and 50 have been recommended for pilot and feasibility studies [24,25]. A power analysis for a within-groups repeated measures analysis of variance (ANOVA) with 0.8 power, a medium effect size and 3 measures (baseline, 1 week after the start of the intervention, 3 months after the start of the intervention) yielded a size of 20. With a drop-out rate of 30% we will need a minimum of 31 people. Participants will need to live in the North Central London (NCL) Integrated Care System (ICS) area. We will identify potential participants through participant identification centres (NHS trusts) that are accessed by people with CP. Recruitment will also be conducted by the research team via social media channels and through distribution of leaflets in community-based organizations operating in NCL.

For the key stakeholders and supporters sample we will invite people involved in the development or delivery of the intervention to take part in semi-structured interviews to share their feedback on the CP Link Worker intervention. Individuals who have held one of the following roles will be eligible: link worker, community-based service providers to whom participants were referred as part of the social prescriptions, participant’s carer/ supporter, or UP founder involved in the training and supervision of the link worker.

This study will recruit participants into the intervention from 21/01/2026 until 31/10/2026. Data collection will be completed by January 2027 and data analysis will be completed by April 2027.

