#### Link worker intervention.

The intervention will involve a specialised link worker role based in NCL for a period of 12 months. This link worker will receive bespoke training on living and ageing with CP plus any additional training needs identified by themselves and UP (e.g., motivational interviewing). Following this they will work in the NCL ICS. The link worker will work with adults with CP to determine their individual non-medical needs and then link them into community resources that could support them to improve their health and wellbeing. The process of the link worker intervention is provided in Fig 1.

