**Fig 1 pone.0343206.g001:**
[figure not shown]
Flowchart of the link worker intervention, including recruitment, data collection, and intervention phases.

Once informed consent is provided to the postdoctoral researcher (ER), the link worker will contact the eligible participant to arrange the introductory phone call and will send them either the link or the paper version of the baseline questionnaire, which must be completed before the intake meeting. During the introductory phone call the link worker will answer any questions the participant may have in relation to their role and will check whether the baseline questionnaire has been completed. If the survey has not been completed, the link worker will provide assistance before moving forward. If the participant has questions about the study itself, the researcher will be available to answer these and, if needed, arrange a separate meeting with the participant.

After the introductory phone call, the link worker will schedule the intake meeting. This can take place in person, over the phone, or via computer (video call), depending on the participant’s preference. During the intake meeting, the link worker will work with the participant to identify their non-medical needs and main priority areas, and to establish an agreed set of priority goals to be achieved within the intervention. Goals will be tailored to each participant’s needs and should follow the SMART principle – Specific, Measurable, Attainable, Realistic and Timely – with the overall aim of supporting the participant’s wellbeing. To help focus the discussion and ensure areas of needs are prioritised, participants will be asked to identify their top two concerns using a structured tool, based on Goal Attainment Scaling [27] and adapted from existing practice. This tool provides a guide to support the identification and prioritisation of needs, while also allowing flexibility to address other areas the participant wishes to raise. The process of identifying and prioritizing non-medical needs and goals will remain participant led. The intake meeting will last approximately 1 hour.

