#### Data collection.

The number of people invited to take part in the intervention, those who self-refer, the number of participants enrolled in the programme, and retention rates will be recorded by the researcher throughout the intervention period.

Data will be collected from participants through survey at three time points – baseline, 1-week, and 3-month follow-up – and through a voluntary-based interview at the end of the intervention. Participants will be able to complete the survey either online or on paper. Participants will be asked to complete the survey within one week of receiving it. Participants who require additional support may choose to complete the survey with assistance from their carer/ supporter, the link worker, or request a paper version of the questionnaire by post. The questions asked at baseline, 1-week and 3-months are outlined in Table 1.

**Table 1 pone.0343206.t001:** Data collected from intervention participants.

Domain	Measure	Baseline questionnaire	Intake meeting	1-week follow up questionnaire	3-month follow up questionnaire
Sociodemographic and clinical information	Study-specific items	✓	–	–	–
Use of health and social care services	Use of health and social care services (Understanding Society survey)	✓	–	–	✓
Achievement of participant goals	Goal Attainment Scaling – light model (GAS- Light) [27]	–	✓	–	✓
Psychological wellbeing	World Health Organization-Five Well-Being Index (WHO-5) [32]	✓	–	–	✓
Health related quality of life	EuroQol 5-Dimension 5-Level (EQ-5D-5L) [33]	✓	–	–	✓
Loneliness	UCLA-3 item Loneliness Scale (UCLA-3item) and a direct question about how often the respondent feels lonely [34]	✓	–	✓	✓
Fatigue	One-Item Fatigue Screen (OIFS) [35]	✓	–	✓	✓
Pain	Single item from EQ-5D-5L [33]	✓	–	–	✓
Social network	Lubben social network scale [36]	✓	–	–	✓
Social group membership and sense of local community	Selected items adapted from [37]	✓	–	✓	✓
Empowerment	Adapted version of the Diabetes Empowerment Scale – Short Form (DES-SF) [38] Individual community-related empowerment scale: Dimension 2 (intention) and 3 (participation) [39]	✓	–	✓	✓
Feedback on the experience with the link worker	NHS Patient Social Prescribing Link Worker Feedback [40]	–	–	✓	✓ (*)
Feedback on social prescription	Study-specific items	–	–	–	✓ (*)
Feedback on the overall intervention	Study-specific items	–	–	–	✓ (*)

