After completing the 3-month follow up questionnaire, all participants will be invited to take part in an interview with the research team to discuss their expectations of the intervention, their experiences with the link worker, and the activities to which they were referred. The interview will also explore their views on what worked well and what could be improved. Participation is voluntary, and refusal will not affect involvement in the study. The interview will be conducted either online, over the phone, or in-person depending on the preference of the interviewee and will last around 60 minutes. To help reduce potential anxiety, the list of interview questions will be shared with interviewees one day before the interview. The accompanying message will clarify that no preparation is required for the interview unless the interviewee chooses to do so. Interviewees will also be able to contact the research team up to one week after the interview to share any additional thoughts or reflections.

Withdrawal from the intervention will be defined as either an explicit decision communicated by the participant (or their carer/ supporter) to the research team to discontinue their involvement (active withdrawal) or non-engagement despite repeated follow-up attempts (passive withdrawal). Passive withdrawal will be defined as non-engagement after three unsuccessful follow-up attempts by the link worker within one month, using a combination of methods (phone, email, and post). No further contact will be made by the link worker after this point. Withdrawal may occur at one of three stages: prior to the introductory phone call with the link worker, after receiving the social prescription, or during the 3-months follow-up period for data collection. In the event of participant withdrawal, the research team will invite participants to complete a brief withdrawal questionnaire online or on paper to capture the reason for disengagement and gather feedback on the intervention. In case of non-engagement, the reason for withdrawal will be recorded as unknown.

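### The January 2027 close of data collection leaves no slack for the last recruits' 3-month questionnaire and no room for their interview

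*Protocol article*

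**What the plan says.** The calendar is in the Protocol article, Participants and recruitment. Recruitment and close: "This study will recruit participants into the intervention from 21/01/2026 until 31/10/2026. Data collection will be completed by January 2027". Analysis is to finish by April 2027. No day in January is given. The same section times the last survey at "3 months after the start of the intervention", so the clock does not start at consent.

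The other sections add steps on either side of those 3 months:

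- Before intake (Link worker intervention, text under Fig 1): consent, then an introductory call, and a baseline questionnaire that has to be in hand first ("the paper version of the baseline questionnaire, which must be completed before the intake meeting"). No time limit is set for reaching intake.
- After the 3-month point (Data collection): "Participants will be asked to complete the survey within one week of receiving it". Then: "After completing the 3-month follow up questionnaire, all participants will be invited to take part in an interview". Interviewees receive the questions one day ahead and may send further thoughts for up to a week afterwards.

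The intervention is described as "a specialised link worker role based in NCL for a period of 12 months", with support for each participant lasting at most three months. The start date of the role is not given.

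**The concern.** Two fixed dates, the end of recruitment and the end of data collection, are three months apart. The follow-up pathway for one participant takes three months plus several further steps. If the dates are followed as written, the people recruited last have their follow-up cut short by the calendar and not by any choice of theirs.

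This touches what a feasibility study is meant to measure. Retention and completeness of outcome data are named feasibility outcomes. Acceptability relies on the 3-month questionnaire and the interviews. Goal attainment is recorded only at intake and at 3 months, so a missing 3-month record leaves no follow-up rating for that person. If truncated follow-up were mixed with true disengagement, the retention and completeness figures would understate what the service and the data collection can achieve.

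**Working it through.** **Inputs from the article:** recruitment from 21 January to 31 October 2026 (284 days, counting both ends); last survey 3 months after intervention start; 7 days to return it; interview after the questionnaire, with questions sent 1 day before; 7 days for reflections; target of 31.

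**Assumptions:** a delay of 0, 14 or 28 days from consent to intake (none is stated); intake taken as the start of the intervention; interview the day after the questionnaire is returned, the shortest gap that allows questions to be sent a day ahead; even accrual; data close on 1 or 31 January 2027, the two ends of the stated month.

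**Step 1: the plan's own dates.** 31 October 2026 + 3 months = 31 January 2027. On the most generous reading the slack is 0 days.

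**Step 2: the last recruit.** Finish = 31 October 2026 + delay + 3 months + 7 days (return) + 1 day (interview) + 7 days (reflections).

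| Delay to intake | Survey due | Return week ends | Interview | Reflections end |
|---|---|---|---|---|
| 0 days | 31 Jan 2027 | 7 Feb | 8 Feb | 15 Feb |
| 14 days | 14 Feb 2027 | 21 Feb | 22 Feb | 1 Mar |
| 28 days | 28 Feb 2027 | 7 Mar | 8 Mar | 15 Mar |

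The stated January 2027 completion is not reproduced under any of these delays.

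**Step 3: how many are affected.** Latest workable consent date = close − 1 day − 7 days − 3 months − delay. Share too late = days of recruitment after that date ÷ 284. Expected number = share × 31.

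| Close | Delay | Latest consent | Days too late | Share | Of 31 |
|---|---|---|---|---|---|
| 31 Jan 2027 | 0 | 23 Oct 2026 | 8 | 2.8% | 0.9 |
| 31 Jan 2027 | 14 | 9 Oct 2026 | 22 | 7.7% | 2.4 |
| 31 Jan 2027 | 28 | 25 Sep 2026 | 36 | 12.7% | 3.9 |
| 1 Jan 2027 | 0 | 24 Sep 2026 | 37 | 13.0% | 4.0 |
| 1 Jan 2027 | 14 | 10 Sep 2026 | 51 | 18.0% | 5.6 |
| 1 Jan 2027 | 28 | 27 Aug 2026 | 65 | 22.9% | 7.1 |

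These counts leave out the reflection week. Adding it for a 31 January close raises the shares to 5.3%, 10.2% and 15.1% (1.6, 3.2 and 4.7 of 31).

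**Step 4: the questionnaire alone.** If every questionnaire were returned on the day it fell due and the close were 31 January, the shares too late would be 0 of 284 days at no delay, 14 ÷ 284 = 4.9% (1.5 of 31) at 14 days and 28 ÷ 284 = 9.9% (3.1 of 31) at 28 days.

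**The case against.** Five points can be made on the other side.

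- **The questionnaire can just fit.** A reader might infer that late recruits cannot complete the 3-month questionnaire at all. That goes too far. With intake on the day of consent and a close on 31 January, someone recruited on 31 October could complete it on its due date; the week for return is a maximum. This stands, but it needs every step to take no time, and the interview still does not fit.
- **Nothing says these people are counted as lost.** A reader might infer that they would be recorded as drop-outs. The article defines withdrawal as an explicit decision or as non-engagement after three failed attempts within a month, and a person cut off by the calendar meets neither. A denominator rule may also sit in a fuller protocol or analysis plan that is not shown. So a downward bias in retention is possible, not established.
- **The sample size is not undermined.** It is tempting to say that the allowance of 31 × 0.7 = 21.7 against 20 is used up by two truncated participants. It is not: 29 × 0.7 = 20.3. The 31 is a minimum recruitment target, and the analysis section describes summaries and thematic analysis.
- **Interviews are voluntary, with no target number.** True, and losing a few does not bias a quantitative outcome. But all participants are to be invited, and under these dates the last ones could not be interviewed before the close.
- **Link worker cover.** If the 12-month role began with recruitment on 21 January 2026, it would end about 20 January 2027, before the last recruits' support window closes. The start date is not stated, so this is a point to check and not a demonstrated conflict.

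**Conclusion.** The conflict in the dates is real and follows from the article's own text. For the last recruits there is no slack for the questionnaire and no room for the interview, and the full pathway runs to about 15 February 2027 with no delay to intake and to 1–15 March with a delay of two to four weeks.

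The size is modest: about 1–4 of 31 for a close on 31 January and about 4–7 of 31 for a close on 1 January. Those ranges rest on even accrual, an assumed 0 to 4 week delay and a next-day interview. Recruitment weighted towards the end of the window would raise them; faster early recruitment would lower them. The affected participants may appear as incomplete in the retention and completeness rates, since the article does not say how they are handled. Severity: should-fix.

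**What to change.** Move the end of data collection to about mid to late March 2027 and leave the end of analysis at April 2027. That covers the last recruit with a delay of up to four weeks (15 March). The cost is a shorter analysis window for a small, descriptive dataset: taking 30 April as the end, it falls from 89 days after 31 January to 46 days after 15 March, or 30 days after 31 March. The last interviews would need prompt transcription.

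If the January close is kept, give its exact day and state that participants whose 3-month point falls after it are reported separately and left out of the 3-month retention and completeness denominators. This costs one sentence.

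Ending recruitment earlier would also reconcile the dates, but it gives up the very recruits whose follow-up would be truncated, and recruitment is itself a feasibility outcome.

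In either case, check the link worker's 12-month period and the support window of up to three months against the same dates, and reconcile those passages. If the role has to be extended, that needs resources beyond a change of date.
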